### Intervention arm: the thriving Mamas programme

The Thriving Mamas programme aims to support adolescent girls’ wellbeing during pregnancy and the year after birth. The programme consists of nine meetings delivered in either group (5 meetings), individual (1 meeting), or family group (2 meetings) formats over 10 weeks with an additional individual meeting 10–12 weeks postpartum (see Fig. 3). The intervention will be provided in addition to usual perinatal care. Each meeting focuses on physical and mental health, taking care of a newborn, life skills, planning for the future, and harnessing social support. Girls identified as requiring additional support will be referred to health and community-based services. The programme is facilitated by 1–2 women recruited from the local community who have been previously pregnant. Meetings will take place in a mixture of private settings in health facilities, community facilities, and participant homes. Each meeting will last between one and two hours. All mentor mothers will receive training over three to five days to deliver the programme.

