### Control arm

Adolescents randomised to participate in the control arm of the trial will receive usual care provided in each country. Each visit includes care that is appropriate to the overall condition and stage of pregnancy and should include four main categories of care:Identification of pre-existing health conditions.Early detection of complications arising during pregnancy.Health promotion and disease prevention.Birth preparedness and complication planning.

In both arms, all participants will be screened for depression and anxiety during pregnancy and after participation in intervention sessions. Adolescents who screen positive for depression or anxiety will be referred for further assessment and care, where needed. Disclosure of or suspected gender-based violence will be provided with information on their rights and where to seek support based on local care provision in each country.

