**Intervention content and delivery**														
*Recruitment rate*	Programme notes			X										
*Retention rate*	Programme notes				X	X	X	X	X	X	X	X	X	
*Referral Rate*	Programme notes			X				X					X	
*Acceptability*^a^	Acceptability of Intervention Measure (AIM) [4]		X											X
*Feasibility*^a^	Feasibility of Intervention Measure (FIM) [4]		X											X
*Appropriateness*^a^	Intervention Appropriateness Measure (IAM) [4]		X											X
*Fidelity*^a^	Adolescent retention rate (fidelity of receipt)				X	X	X	X	X	X	X	X	X	
	Enhancing Assessment of Common Therapeutic Factors (ENACT) [10] (delivery fidelity; collected from adolescent girls)												X	
*Cost of intervention*	Time taken to be trained and deliver the intervention; cost of materials for delivery		X											X
*Qualitative Interview*	Semi-structured interview		X											X

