**Health and wellbeing**														
*Depression*^a^	Patient Health Questionnaire (PHQ-9) [9]			X				X					X	
*Anxiety*^a^	Generalised Anxiety Disorder (GAD-7) [7]			X				X					X	
*Quality of life*^a^	WHO Quality of Life short version (WHOQoL-BREF) [26]			X										X

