**Health behaviours**														
*Perinatal appointment attendance*^a^	Information on attendance to appointments will be based on self-report by adolescent girls			X				X						X
*Referral uptake*^a^	Information on attendance to appointments will be based on self-report by adolescent girls													X
*Infant vaccination*	Health behaviours questionnaire [1]			X										X
*Breastfeeding*	Health behaviours questionnaire [1]			X										X
*Intended time to next pregnancy*^a^	Health behaviours questionnaire [2]													X
*Contraceptive use*^a^	Health behaviours questionnaire [2]													X

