#### Adolescent girls

A variety of variables will be collected from adolescents by mentor mothers and/or a member of the research team at pre-intervention, meeting 4 and post-intervention to investigate the impact of the intervention.*Depression*: Depression is the primary outcome for our study. The Patient Health Questionnaire (PHQ-9; [26, 27]) is a self-administered screening instrument for common mental disorders. The PHQ-9 is the depression module, which scores each of the 9 DSM-IV criteria as “0” (not at all) to “3” (nearly every day). The PHQ-9 has been validated in Kenya [28] and Mozambique [29].*Anxiety*: The Generalised Anxiety Disorder (GAD-7) measure is a seven-item screening tool for anxiety disorder. Each item scores a symptom of anxiety from “0” (not at all) to “3” (near every day). A GAD-7 score ≥ 10 indicates moderate to severe anxiety. The GAD-7 has been validated in Kenya [30] and Mozambique [31].*Quality of life*: Quality of life will be assessed using the short version of the WHO Quality of Life brief version (WHOQOL-BREF; [32]). The WHOQOL-BREF assesses a respondent’s perceived quality of life across four domains: physical health; psychological; social relationships; and environment. Its 26 items are scored on a five-point Likert scale with higher scores indicating greater agreement. The items are allocated to each domain to provide domain scores with higher scores indicating greater quality of life in a particular domain. The WHOQOL-BREF has been used with adolescents in Kenya [33].*Social support*: The Multidimensional Scale of Perceived Social Support (MSPSS) is a 12-item scale which measures social support from family, friends, and significant others [34]. Each item scores the extent to which the respondent agrees with the statements on a Likert scale with “1” (very strongly disagree) to “7” (very strongly agree). The scale has been validated in adolescents in Ghana [35].*Parenting competency*: The Parenting Sense of Competency Scale is a 17-item scale to measure parents’ perceived parenting abilities [36]. The items are rated on a 6-point Likert response scale from “strongly disagree” to “strongly agree.” Overall parenting competence is derived from a total score where higher scores indicate greater perceived competence. The scale has been used to evaluate parenting competence among mothers of infants aged 2–12 months [37, 38].*Service utilisation*: Antenatal appointment attendance information will be collected from adolescent girls through two questions (i.e. How many antenatal appointments were you scheduled to attend since our last meeting? How many of those appointments did you attend?). Uptake of referrals to community services will be collected from adolescent girls through three questions (i.e. Have you been referred to any community services by your intervention provider? If yes, which services have you been referred to? If yes, have you made contact with these services?).*Health behaviours*: Family planning intentions will be assessed using quantitative questions regarding actual or intended contraception use and intended time to next pregnancy. Actual or intended breastfeeding and infant vaccinations will also be collected through a single question for each variable to determine the impact of the intervention on these behaviours.*Provider competency*- The Mentor mothers’ competency will be assessed using the ENACT tool which was adapted to improve relevance to the study. ENACT tool measures a set of therapeutic competencies required for the effective intervention, including the delivery by the non-specialists [39].

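### Referral uptake is asked once, at an undated Post assessment, in wording that leaves out health-service referrals and does not fit control girls

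*Protocol article*

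**What the plan says.** Both arms have a referral pathway. The section on the Thriving Mamas programme states "Girls identified as requiring additional support will be referred to health and community-based services". The Control arm section, in a paragraph that applies to both arms, states "Adolescents who screen positive for depression or anxiety will be referred for further assessment and care, where needed".

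Table 1 lists "Referral Rate" under Intervention content and delivery, marked at Pre, meeting 4 and meeting 9. PHQ-9 and GAD-7 carry the same three marks. Table 1 lists "Referral uptake" under Health behaviours, by self-report, with a single mark at Post.

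The text on service utilisation, in the Adolescent girls part of the variables section, says "Uptake of referrals to community services will be collected from adolescent girls through three questions". The first of the three is "Have you been referred to any community services by your intervention provider"; the other two ask which services and whether contact was made. No timing is given for them. The lead-in to the same part says in general terms that girls' variables are collected before the intervention, at meeting 4 and after the intervention.

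**The concern.** Referral uptake is a listed outcome of a pilot whose purpose is to refine procedures for a full trial. No other quantitative source of uptake is described: mentor mother meeting records are named as the source of referral rates, not of whether the girl reached the service.

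A single late question creates three difficulties.

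- It mixes referrals that are months old with referrals made at the last screen. None of the three questions asks when the referral was made, so a low figure could mean a weak pathway, poor recall or too little time, and the item cannot tell these apart.
- It depends on the girl still being in the study at Post.
- Its wording covers only part of the referrals that the protocol itself describes, and it presupposes an intervention provider, so an uptake figure for the control arm has no clear meaning.

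**Working it through.** The protocol gives no figure for the delay between referral and the uptake question, so there is none to reproduce. The delay is derived below.

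**Schedule.** Table 1 has 13 timepoint columns: training Pre and Post; intervention Pre, meetings 1–9, and Post. The meeting count agrees with the programme text: 5 + 1 + 2 + 1 = 9. The marks are:

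| Item | Timepoints |
|---|---|
| Referral rate | Pre, meeting 4, meeting 9 |
| PHQ-9, GAD-7 | Pre, meeting 4, meeting 9 |
| Perinatal appointment attendance | Pre, meeting 4, Post |
| Referral uptake | Post |

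The neighbouring attendance item is asked three times and refers to the period since the last meeting. Referral uptake is not handled that way, and its single mark does not match the lead-in's general timing.

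**Inputs from the protocol.** Entry is up to 28 weeks' gestation. Eight meetings take place over 10 weeks, and meeting 9 is 10–12 weeks postpartum. Data collection is projected from October 2023 to May 2024; 1 October to 31 May is 243 days, or 243/7 = 34.7 weeks (8.0 months).

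**Assumptions not in the protocol.** Birth is at 40 weeks (37–42 shown as a range), meeting 4 falls about 4–5 weeks after Pre, and Post is at or after meeting 9. One month is 365.25/12/7 = 4.35 weeks.

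**Pre referral to meeting 9, the earliest that Post can be:** (40 − gestation at entry) + 10 to 12 weeks.

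- Entry at 28 weeks: 12 + 10 to 12 = 22–24 weeks (5.1–5.5 months).
- Entry at 20 weeks: 20 + 10 to 12 = 30–32 weeks (6.9–7.4 months).
- Upper limit: the window of 34.7 weeks (8.0 months). A girl enrolled on 1 October would have to be at least 40 − (34.7 − 10) = 15.3 to 40 − (34.7 − 12) = 17.3 weeks pregnant to reach meeting 9 by 31 May.
- For entry at 28 weeks, birth at 37 weeks gives 19–21 weeks (4.4–4.8 months), and birth at 42 weeks gives 24–26 weeks (5.5–6.0 months).

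**Meeting-4 referral to meeting 9:** subtract 4–5 weeks.

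- Entry at 28 weeks: 22 − 5 = 17 to 24 − 4 = 20 weeks (3.9–4.6 months).
- Upper limit from the window: 34.7 − 5 = 29.7 to 34.7 − 4 = 30.7 weeks (6.8–7.1 months).

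**Meeting-9 referral to Post:** not stated. It could be zero. At most, for a girl who enters at 28 weeks on 1 October and has Post on 31 May, it is 34.7 − 24 = 10.7 to 34.7 − 22 = 12.7 weeks.

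**Loss before Post:** 0.33 × 80 = 26.4, about 26 girls. How many of them would have been referred is unknown.

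**Wording against referral rules.**

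| Aspect | Referral text | Uptake item |
|---|---|---|
| Services | Health and community-based; further assessment and care | Community only |
| Referrer | Not limited | Intervention provider |
| Arm | Both | Presupposes the intervention arm |

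**The case against.** The strongest reply is that this is one descriptive secondary item in a pilot of 80 girls. It is neither among the implementation outcomes that the Data analyses section calls primary nor among the progression criteria, and how often to ask it is largely a design preference. The last question is cumulative, so Post can still capture an early referral that was taken up. Uptake is also a qualitative interview topic. All of this stands and limits the weight of the point. It does not make the pooled figure interpretable, and it does not answer the mismatch in wording.

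A reader might infer more than the protocol supports, in four ways.

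- **A delay of up to 9 months.** Entry at 12 weeks would give 38–40 weeks (8.7–9.2 months), which exceeds the projected window of 34.7 weeks.
- **Little or no time for meeting-9 referrals to be taken up.** Post is a separate, undated column. A short gap is possible, but so is one of several weeks. Only an unstated and shorter opportunity can be asserted.
- **A calculable bias.** With referrals spread evenly over three screens and no uptake after the last, a true 60% would read as (0.60 + 0.60 + 0)/3 = 40%. The protocol supports neither condition, and the item is answered per girl, not per referral.
- **Unmet referrals go undetected and nobody can act.** PHQ-9 and GAD-7 are repeated at meeting 4 and meeting 9, intervention girls meet mentor mothers repeatedly, and local coordinators keep in touch with data collectors, mentor mothers and girls. Follow-up of referrals is neither described nor excluded, and an article may leave it to the full protocol.

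**Conclusion.** The point holds as a measurement weakness. Uptake is asked once, at Post, for referrals arising at three timepoints. The first question comes roughly 5–8 months after a Pre referral and roughly 4–7 months after a meeting-4 referral. These ranges rest on birth at 40 weeks, meeting 4 at about week 4–5 and the projected October–May window; birth at 37 weeks would lower the bottom of the Pre range to about 4.4 months. The opportunity after a meeting-9 referral is shorter and cannot be determined from the protocol. With the planned loss to follow-up, about a third of girls would give no uptake answer.

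The mismatch in wording needs no assumption: health-service referrals fall outside the item, and control girls have no intervention provider to whom it could refer. The change is worth making because it is cheap and improves a listed outcome. No primary result depends on it, and it is not evidence that girls' safety is compromised.

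**What to change.** - In Table 1, mark the referral questions also at meeting 4 and meeting 9, and at the matching control assessments, each time about referrals since the previous assessment. Keep the Post question.
- Reword the questions to cover health and community services and any referrer, so that they work in both arms.
- State when Post takes place relative to meeting 9, and bring the lead-in's general timing into line with Table 1.
- Report uptake by the screen at which the referral was made, with last-screen referrals shown separately.

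The cost is a revised Table 1 and questionnaire and a few minutes of interview time at assessments already scheduled. How unmet referrals should be managed clinically is outside this recommendation.

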#### Adolescent girls

Up to 40 adolescent girls will be recruited in each country (*n* = 80), through participating community services and health facilities. In Kenya, adolescents will be recruited from local dispensaries. In Mozambique, adolescents will be recruited from primary health centres. The following inclusion criteria will be used: (a) up to 28 weeks pregnant; and (b) aged 15–19 years. They will be excluded from the study if they are unable to provide informed consent or are unable to participate in the intervention, due to existing health conditions.

Adolescent girls who meet the study inclusion criteria will be given information about the study by health facility staff. Those interested in participating will be introduced to a member of the research team, who will provide them with an information sheet and consent form. Where an adolescent is aged 15–17 years, the research team also will discuss the information with their guardian during the same visit, if the guardian is in attendance. If the guardian is not present, a member of the research team will discuss the information sheet with the minor. If she indicates further interest in participating, we will explain that we also require guardian consent due to her age. Following introduction to their guardian, the study will be introduced using the information sheet and consent requested. In this situation, the minor will be required to provide their assent following guardian consent.

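### The referral-uptake items ask only about community services, so uptake of health-service referrals may go unrecorded

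*Protocol article*

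**What the plan says.** The service-utilisation entry in the protocol article (Variables and data collection procedures, Adolescent girls) introduces the measure as follows: "Uptake of referrals to community services will be collected from adolescent girls through three questions". It then prints the questions:

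1. "Have you been referred to any community services by your intervention provider"
2. "If yes, which services have you been referred to"
3. "If yes, have you made contact with these services"

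The section on the intervention arm describes where girls are sent: "Girls identified as requiring additional support will be referred to health and community-based services". The Control arm section, in a paragraph that covers both arms, adds: "Adolescents who screen positive for depression or anxiety will be referred for further assessment and care, where needed".

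Table 1, under health behaviours, lists referral uptake without limiting it to one kind of service. It is marked at the Post timepoint only, and its source is given as "Information on attendance to appointments will be based on self-report by adolescent girls". The number of referrals made is a separate variable, the referral rate, taken from programme notes and mentor mother meeting records.

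**The concern.** The first question decides whether the other two are asked. It names one of the two kinds of destination to which the programme refers girls. A girl sent only to a health service can truthfully say no, and the sequence stops there.

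What is at stake is whether the pilot can report how often girls sent to health care make contact with it. The programme concerns perinatal mental health, and girls with a positive depression or anxiety screen are referred for more help. The pilot exists to refine procedures for a full trial, so a variable that covers only part of the referral pathway gives that trial only part of what it needs. Referral uptake is neither a primary outcome nor a progression criterion, so the consequence is limited to this one measure.

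**Working it through.** The article states no figure for referral uptake, so there is nothing to reproduce. The check is a comparison of the text.

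**Step 1: scope of the referrals.** The intervention-arm section names health services and community-based services as destinations. The paragraph on screening refers screen-positive girls in both arms for more evaluation and treatment. It does not name the destination.

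**Step 2: scope of the question.** The lead-in and the first item both say community services only. The questions are printed in full after *i.e.*, so the article fixes their wording.

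**Step 3: does the article use community services to include health services?** Its own usage suggests not. The intervention-arm section names the two kinds side by side. The recruitment text for adolescent girls does the same: "through participating community services and health facilities".

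**Step 4: is health-referral uptake captured elsewhere?**

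| Source | What it gives | Uptake of health referrals? |
|---|---|---|
| Three referral items (Post) | Community referrals and contact | Not as worded |
| Programme notes and mentor mother records | Referrals made | No, not contact |
| Antenatal appointment items | Appointments scheduled and attended | No, not referrals |
| Qualitative interview topic (Table 1, footnote a) | Narrative account | Possibly, but not a rate |

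**Step 5: the contact question.** Item 2 allows several services to be named. Item 3 is printed once, for all of them together. The antenatal items in the same paragraph ask for a number scheduled and a number attended, so a proportion can be formed. The referral items as printed do not ask for counts. No response format or scoring rule is given.

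An illustration shows when this would matter. Assume that a girl has *k* referrals, that each is contacted independently with probability *p*, and that item 3 takes one yes/no answer. None of these comes from the article. The chance that she contacted some but not all services, so that neither answer fits, is 1 − p^k − (1 − p)^k.

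- k = 2, p = 0.3 or 0.7: 1 − 0.09 − 0.49 = 0.42
- k = 2, p = 0.5: 1 − 0.25 − 0.25 = 0.50
- k = 3, p = 0.3 or 0.7: 1 − 0.027 − 0.343 = 0.63
- k = 3, p = 0.5: 1 − 0.125 − 0.125 = 0.75

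At k = 2 and p = 0.5, uptake would be 1 − 0.5² = 75% if any contact counts and 0.5² = 25% if all must be contacted. This shows only that the rule would matter if one answer were taken.

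**The case against.** **The restriction may be deliberate or harmless.** The lead-in itself says community services, so the measure may be meant to be narrow. The data come from interviews, and a girl or interviewer may take a local dispensary to be a community service. Both are possible. In the first case, Table 1's general title claims more than the items measure and health-referral uptake is not measured at all. In the second, some health referrals are counted and some are not, depending on how each girl understands the term. Neither reading removes the need to reword.

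**The interviews cover it.** Referral uptake is a qualitative topic, and qualitative findings are to be triangulated with the quantitative data. This softens the gap, because contact with health services can come up there. It does not give a rate.

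**Response format and scoring belong in the questionnaire or analysis plan.** This stands. The answer may well be recorded for each service named in item 2. A reader might infer that girls with several referrals are misscored, but the article does not support that. It supports only that item 3 could be ambiguous for them.

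**Uptake is not shown to be understated.** A reader might divide recorded uptake by the referral rate from programme notes and conclude that it is biased downwards. The article plans no such ratio and does not say which referrals the notes count. The items can supply their own numerator and denominator, both limited to community services. Whether community uptake lies above or below health-service uptake is unknown, so no direction can be claimed.

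**Nor can the loss be sized from the background section.** Its estimate that 1 in 3 adolescents has a mental disorder in the perinatal period is not a screen-positive rate or a referral rate, and onward referral is made only where needed. Any share of lost referrals built on it would reflect assumed counts.

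**Conclusion.** The scope mismatch holds on the printed text. The programme refers girls to health services as well as community services, the opening item asks only about the latter, and no other quantitative item records whether girls took up a health referral. Followed as written, the variable would not cover health-service referrals.

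This rests on one assumption: that respondents separate community services from health services as the article itself does. The number of girls affected cannot be computed, since the article gives neither the number nor the mix of referrals. The ambiguity of the contact question is a lesser, conditional point that depends on a response format not shown. The point concerns one secondary, descriptive measure and does not touch the pilot's primary outcomes or progression criteria.

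**What to change.** - Reword the first item to ask about referral to any health or community service.
- Keep the second item as the list of services. Record contact separately for each service listed.
- Report uptake as services contacted divided by services the girl reports being referred to, with health and community services shown separately.
- Use the girls' own reported referrals as the denominator. Mentor mother records cannot serve for control girls, who have no mentor mother meetings.

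The first item also ties the referral to an intervention provider, which control girls do not have. That is a separate matter and this point does not rest on it, but it can be settled in the same rewording if the item is to be put to both arms.

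The cost is a change to one interview form and about one extra minute for girls with more than one referral. The article reports that no participants had been recruited as of September 2023. If the form was used unchanged, the result should be labelled as uptake of community-service referrals only, and the new wording carried into the full trial.
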